## **4. STUDY POPULATION**

### ***4.1 Population (base)***

Subjects eligible for participation in the study must be adults with postlingual SSD due to cochlear damage. General practitioners and ENT-specialists in hospitals near Utrecht will be informed about the study and asked to inform and refer potential subjects with SSD to the ENT department of the UMC Utrecht.

## **4.2 Inclusion criteria**

- Patients aged 18 or older.
- Acute onset of postlingual SSD, defined as onset unilateral hearing loss between  $\geq 3$  months and  $\leq 10$  years before time of inclusion.
- Hearing measurements:
  - Pure Tone Audiometry of the deaf ear, defined as thresholds of 70 dB or higher on frequencies 0,5 – 4.0 kHz (average).
  - Normal hearing on the contralateral ear, defined as pure tone audiometry thresholds of 30 dB or less on frequencies 0.5 – 4.0 kHz (average).
  - Air bone gap  $\leq 10$  dB.
- Normal function of middle ear (i.e. no acute middle ear infections or tympanic membrane perforations).
- Dutch language proficiency.
- Willingness and ability to participate in all scheduled procedures outlined in the protocol.
- General health allowing general anaesthesia for the potential surgical implantation of a CI or BAHA.
- Patients covered by the Dutch health insurance.
- Patients should agree to be implanted with a CI or BAHA.
- Informed consent understood, filled out and signed by patient.
- Patients are not allowed to participate in another ongoing research study related to SSD or cochlear implantation.

## **4.3 Exclusion criteria**

- Previous experience with implanted BAHA or CI.
- Retrocochlear pathology.
- Abnormal cochlear anatomy in one or both ears (i.e. ossification).
- Disability which could interfere with the completion of the tests (i.e. psychiatric problems (e.g. auditory hallucinations could negatively affect performance on tests or questionnaires)), based on medical history as assessed by clinician and in electronical patient file.
- Severe comorbidity with an expected survival of less than five years, based on medical history as assessed by clinician and in electronical patient file.

## **4.4 Sample size calculation**

To detect a clinically relevant difference of 5 dB SNR (standard deviation 5 dB) between the groups on the modified Plomp test, with an alpha of 0.05 and a power of 95%, 27 subjects

per group are needed. To be safe, a 10% margin is used to compensate for potential dropouts (e.g. non user cochlear implantees), resulting in 30 patients in the CI group. From recent literature we know that 55% of BAHA-on-headband users are not satisfied after their trial period and choose not to be implanted with a BAHA (Desmet 2012). Therefore, we must include more patients in groups B and C for compensation of the patients ending up in the 'no treatment' group. According to this proportion, 40 patients will end up with a BAHA. Patients not opting for a BAHA can choose for a CROSS. Based on many years of experience at our Audiologic Center, we expect ~60% to choose for CROSS. Thus, predicted numbers per group will be: CI (30), implanted BAHA (40), CROSS (30), 'no treatment' (20), leading to  $n = 45$  for groups B and C. These numbers allow for a valid calculation of the clinically relevant difference on the modified Plomp test.

Based on figures from the UMC Utrecht (in Dutch: Bedrijfsbureau DHS), approximately 25-30 patients per year with SSD present at the ENT outpatient department. Together with patients from the peripheral area of the UMC Utrecht, we expect the inclusion of patients to last for 3-4 years after the inclusion of the first patient. We also expect single-sided deaf patients from other areas of the country to present at the ENT department at the UMC Utrecht.

## 5. TREATMENT OF SUBJECTS

### ***5.1 Investigational product/treatment***

Before study inclusion, subjects will receive standard workup for the diagnosis SSD. This ENT workup includes a clinical history and interview, otologic examination, audiological testing and a MRI-scan for auditory nerve evaluation. Additionally, to determine eligibility for cochlear implantation, a CT-scan will be made to visualize the anatomy of the mastoid. When the diagnosis SSD is sure, all inclusion criteria are met and anatomy permits cochlear implantation, inclusion and randomisation will take place.

Subjects will be asked to read and sign the Informed Consent form presented by the patient's ENT-surgeon before randomisation. This physician will fill in a Demographics Form to gather subject information.

Baseline evaluation for gathering study related data will take place locally at randomisation:

- Pure tone audiometry
- Speech audiometry (CVC [consonant-vowel-consonant] score in quiet)
- Questionnaires: SSQ, HUI3, GBI, APHAB, TTO, VAS, EQ5D, HADS, and Tinnitus questionnaires.

The patients will be asked to fill in a monthly costs diary starting on the first day after inclusion until the end of the second year of the study. From then on, they will complete the costs diary once per 3 months.

For all patients in group A (CI group) and those in group B or C preferring BAHA implantation preoperative medical evaluation will be carried out locally by the anaesthesiologist and includes a determination of general health status and suitability for surgery. Subjects in the CI group will also be evaluated by the center's Cochlear Implant Team, as is standard care for cochlear implantees. The standard surgical procedures developed for placement of the BAHA and the internal components of the CI will be followed. Specific procedures for implanting of the devices will be left to the discretion of the surgeon.

The first evaluation visit will occur approximately 3 to 7 weeks after surgery in the CI group to custom fit the processor software. It will be programmed for optimal speech perception, based on individual subject preferences.

In the BAHA and CROSS group patients will be evaluated after 6 and 12 weeks (see Figure 1). After finishing both test periods, the patient will be asked with which modality he or she wants to continue; either CROSS, BAHA or no treatment. When a patient chooses CROSS, he or she will be followed up by their own audiologist and returns to the UMC Utrecht for regular follow up sessions in this study. When a patient chooses a BAHA, a definitive BAHA will be implanted during an operation in the skull bone. Postoperative evaluation will take place according to regular BAHA-care procedures (e.g. mounting of abutment 6 weeks postoperatively when there is no skin reaction and software set up). Patients choosing no treatment will only be seen during the specified study follow up sessions.

In all treatment groups, standard evaluation sessions for collecting data will take place at 6, 12, 18 and 24 months after randomisation. After the first two years, subjects will be evaluated for data collection on yearly basis for three more years (36, 48 and 60 months). All objective evaluation measurements will take place at the UMC Utrecht to ensure that the data are gathered in an identical way. If considered necessary, extra sessions can exceptionally be added.

## ***5.2 Use of co-intervention***

Since we will only include patients with a normal hearing ear on the contralateral side, defined as thresholds of 30 dB or less on frequencies 0.5 – 4.0 kHz, patients shall not use a

contralateral hearing aid. The modalities nowadays used in clinical practice, are within the study protocol, so there is no co-intervention.

## 6. METHODS

### 6.1 Study parameters/endpoints

#### 6.1.1 Main study parameter/endpoint

Performance on modified Plomp test with sentences in Dutch in the individual patient's best aided condition.

#### 6.1.2 Secondary study parameters/endpoints

##### Objective

- Performance on Standard Dutch phoneme perception test (NvA-list)
- Performance on speech intelligibility with spatially separated sources
- Performance on Crescent of sounds test (Quentin Summerfield)

##### Subjective

- Self-reported benefits in everyday listening situations assessed with the Speech, Spatial and Qualities Hearing Scale (SSQ); 63 questions
- Quality-of-life (QoL) questionnaire score:
  - Health Utilities Index 3 (HUI3); 17 questions
  - Glasgow Benefit Inventory (GBI); 18 questions
  - Abbreviated Profile of Hearing Aid Benefit (APHAB); 24 questions
  - Time Trade Off (TTO); 1 question
  - Visual Analogue Scale (VAS); 2 questions
  - Euro-QoL 5D (EQ5D); 6 questions
  - Hospital Anxiety and Depression Scale (HADS); 14 questions
- Tinnitus questionnaires
  - Tinnitus Handicap Inventory (THI); 25 questions
  - Tinnitus Questionnaire (TQ); 52 questions
  - Tinnitus Burden Questionnaire; 12 questions
- Cost utility
  - Costs utility diaries on monthly basis (after 2 years: 3-monthly basis)

### 6.2 Randomisation, blinding and treatment allocation

120 subjects will randomly be assigned to one of the three study groups: 30 in the CI group, 45 in the first-BAHA group and 45 in the first-CROSS group. A website randomisation

program, developed by the Julius Center, UMC Utrecht (<http://www.juliuscentrum.nl/random/>) shall be used to divide the subjects into the groups.

The randomisation chart is established before the start of the study by an independent data manager. When a local executor recruits a subject, the physician can log on to the site and enter the subject's characteristics. A block randomisation model will be used to make sure that the ratio CI:CROSS:BAHA subjects will be about equal ( $30:45:45 = 2:3:3$  per block). The physician will receive an allocation group number on his/her screen within a few seconds. It is only after the subject has signed the Informed Consent form that he/she is randomised and informed of the assigned group.

Logically, blinding is not possible since both patients and doctors will be able to see from the outside whether subjects have received a CI, BAHA or CROSS.

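### Section 6.2 publishes a 2:3:3 block composition in an open-label trial with referral to one department; if blocks are constantly eight, up to 28.6% of patients have a CI or non-CI status that can be known before enrolment

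*Protocol*

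**What the plan says.** Protocol Section 6.2 plans for 120 patients, "30 in the CI group, 45 in the first-BAHA group and 45 in the first-CROSS group". On the method it says "A block randomisation model will be used to make sure that the ratio CI:CROSS:BAHA subjects will be about equal", and in parentheses it reduces 30:45:45 to 2:3:3 and attaches that ratio to each block. It mentions neither varying nor withheld block sizes.

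The same section describes these safeguards and procedures:
- **List:** "The randomisation chart is established before the start of the study by an independent data manager".
- **Delivery:** allocation is through a website. The physician enters the patient's characteristics, and then "The physician will receive an allocation group number on his/her screen within a few seconds". No stratification factor is named.
- **Timing:** "It is only after the subject has signed the Informed Consent form that he/she is randomised and informed of the assigned group".
- **Blinding:** "Logically, blinding is not possible since both patients and doctors will be able to see from the outside" which device a patient has.

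Section 4.1 has general practitioners and ENT specialists refer patients to one ENT department. Section 5.1 adds "All objective evaluation measurements will take place at the UMC Utrecht".

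**The concern.** Blocked allocation is concealed only as long as those who recruit cannot work out what is left in the current block. Here the composition stands in the protocol, allocations cannot be blinded, and recruitment runs through one department. Once both CI places in a block of eight are used, every later patient in that block is known not to receive a CI. Once all six other places are used, the rest are known to receive one.

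Four features of this trial make that matter:
- **Motive.** Section 1.2 says that patients with single-sided deafness are not at present candidates for a CI, whereas BAHA and CROSS are routine care. A patient or physician who hopes for a CI has little reason to enrol when no CI place is left in the block.
- **Opportunity.** Eligibility under Section 4.2 runs from 3 months to 10 years after onset, so most patients can wait without losing it.
- **Discretion.** Sections 4.2 and 4.3 leave willingness, ability and interfering disability partly to clinical judgement, and that judgement precedes randomisation.
- **Sensitivity.** Many secondary outcomes in Section 6.1.2 are self-reported in an unblinded trial, so selection by motivation could affect them.

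At stake is the comparability of the CI group with the other two, which is the reason Section 1.1 gives for choosing a randomised design.

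**Working it through.** **Inputs.** Group sizes 30, 45 and 45 of 120, and the ratio 2:3:3 per block (Section 6.2). Expected inclusion period of 3 to 4 years (Section 4.4). Assumptions, not stated in the protocol: constant block size, one unstratified list, recruiters who know all earlier allocations in the block and where it began.

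**Step 1: the plan's own ratio.** 8 × 30/120 = 2 and 8 × 45/120 = 3, so 2:3:3 is right. 120/8 = 15 complete blocks.

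**Step 2: patients whose CI or non-CI status is certain.** Take a block with *a* CI and *b* non-CI places in random order. The expected number of non-CI places after the last CI place is b/(a + 1). The expected number of CI places after the last non-CI place is a/(b + 1). With a = 2 and b = 6:
- known not CI: 6/3 = 2.000 per block, 2.000/8 = 25.0%, or 15 × 2 = 30 of 120 patients
- known CI: 2/7 = 0.286 per block, 0.286/8 = 3.6%, or 15 × 0.286 = about 4 of 120
- together: 16/7 = 2.286 per block, 28.6%, or about 34 of 120

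Listing all 28 placements of two CI places among eight gives the same 16/7. A simulation of 200,000 blocks gave 28.5%.

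**Step 3: the exact group.** Summing over the three groups, 2/7 + 3/6 + 3/6 = 1.286 per block, and 1.286/8 = 16.1%. The 28.6% therefore concerns CI against not CI, which is the contrast of interest.

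**Step 4: other sizes that fit the same ratio, with the size known to recruiters.**

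| Block size | a, b | b/(a+1) + a/(b+1) | Share certain | Of 120 patients |
|---|---|---|---|---|
| 8 | 2, 6 | 2.000 + 0.286 | 28.6% | about 34 |
| 16 | 4, 12 | 2.400 + 0.308 | 16.9% | about 20 |
| 24 | 6, 18 | 2.571 + 0.316 | 12.0% | about 14 |

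The last column applies each share to 120. If sizes vary at random and are not disclosed, certainty falls further.

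**Step 5: partial knowledge.** The table counts only certain cases. The odds shift as well: a block of eight opens with a CI chance of 2/8 = 25%, but if its first four patients are all non-CI, the next patient's chance is 2/4 = 50%.

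**Step 6: can one wait for the next block?** 120 patients in 3 to 4 years is 40 to 30 a year. A block of eight then lasts 12 × 8/40 = 2.4 to 12 × 8/30 = 3.2 months. Against an eligibility window of years, that delay is practical.

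**The case against.** The strongest reply is that the protocol never says the blocks are fixed or that they hold eight. A 2:3:3 ratio per block is equally true of 4:6:6 and 6:9:9, or of a mixture. The list belongs to an independent data manager, and block lengths are often kept in a restricted document that we cannot see. This stands: eight is the literal reading, not a stated fact, and a reader who takes constant blocks of eight as established goes beyond the text.

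A reader might also infer that the recruiting physician sees every allocation. The documents do not support that. Section 6.2 shows a physician the allocation of the patient just entered. Sections 5.1 and 9.2 have consent presented by the patient's own ENT surgeon and the invitation made by an otorhinolaryngologist, so several people may recruit. A single department makes a shared count feasible but does not establish it. If the entered characteristics are used for stratification, one running count would no longer predict the next patient.

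A third tempting reading is that the resulting bias would be beyond any analysis. That is too absolute. Eligibility is largely audiometric and anatomical, and Sections 3 and 5.1 record baseline characteristics, audiometry and questionnaires, which allow balance checks and partial adjustment. Unmeasured motivation or prognosis would remain.

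What does not stand is the view that the website, the independent data manager and consent before randomisation settle the matter. They hide the list, but they do not stop anyone counting within a block whose composition is published. The decisions on eligibility, invitation and timing all come before login.

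**Conclusion.** The point holds as a conditional one. Publishing the per-block composition in this setting makes part of the allocation foreseeable. Under the literal reading the share is at most 28.6%, about 34 of 120 patients, and seven eighths of that (25.0 of 28.6 points) is knowledge that a patient will not receive a CI. The figure needs four things together: a constant size of eight, one unstratified list, shared knowledge of earlier allocations, and known block boundaries. If the constant size is 16 or 24 it is 16.9% or 12.0%; if any of the other three fails, it is lower.

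The protocol shows that selective or timed enrolment is possible, not that it has happened, and no effect on the modified Plomp test can be estimated from it. This is a cheap improvement to concealment, not a flaw that invalidates the design.

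**What to change.** - Have the independent data manager generate the list, or its not yet used part, with block sizes varying at random in multiples of eight (for example 8, 16 and 24).
- Constrain the sequence so that the total ends at exactly 30:45:45, because freely drawn sizes need not sum to 120. As one illustration, three blocks of 8, three of 16 and two of 24 give 24 + 48 + 48 = 120.
- In Section 6.2, state only the overall 2:3:3 allocation ratio and that block sizes vary and are withheld from recruiting staff. Hold the sizes in a restricted document. Deleting the composition alone would not be enough if blocks are in fact constantly eight, since recruiting staff may already have read it.

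If varying sizes are already in use, only the wording needs to change.

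The cost is a new list, a check that the web program supports varying blocks, and revised wording in Section 6.2. If recruitment has begun, it also takes an amendment under Section 10.2. No patients or visits are added.

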## **6.3 Study procedures**

### **6.3.1 Objective**

#### Modified Plomp test with sentences in Dutch

The Plomp sentence test is designed to determine a patient's ability to understand speech in a noisy environment. This provides a more comprehensive understanding of a person's listening capabilities in daily life than a speech intelligibility test in quiet only. The Plomp test outcome is the critical signal-to-noise-ratio (SNR) at which 50% of sentences is understood correctly. This level is called the Speech Reception Threshold in noise. Both sentences and noise are presented from the front at 70cm distance from the patient.

In the conventional Plomp test a response is considered correct when the presented sentence is repeated without any mistakes. A patient is tested in quiet first to check if the patient is able to perform the task. Although the Plomp test is commonly used in the clinic for patients with mild-moderate hearing loss, it has not been used routinely for cochlear implantees. A speech perception in noise test which is routinely used by a CI-team is a word perception in noise test. The reason for this is that a number of cochlear implant users will not be able to repeat sentences 100% correctly even if presented in quiet. However, in a word test patients cannot use their language ability, as they commonly do in understanding sentences. Therefore we have modified the scoring system of the Plomp test slightly. In the "modified Plomp test" we will be scoring the number of words repeated back correctly instead of the complete sentence. A sentence is considered to be repeated correctly when a subject repeats  $\leq 2$  words of the sentence incorrectly.

Test procedure:

- The sound level that corresponds to the patient's maximum CVC score in quiet (standard procedure) is the individual stimulus level that will be used for the modified Plomp test.
- The starting speech to noise level ratio (SNR) is set to +20 dB (noise 20dB less than individual sound level), at which, in most cases, less than two words per sentence should be repeated back incorrectly.
- The presentation of the noise starts 500 ms before the sentence and stops 500 ms after the sentence.
- If two or less words in a sentence are repeated back incorrectly, the SNR for the next sentence will be decreased by increasing the level of the noise, i.e. the task will be made more difficult. If more than two words are repeated back incorrectly, the SNR will be increased, i.e. the task will be made easier.
- Initially, the SNR will be changed in 10-dB steps. The step size will be reduced to 5 dB after one reversal and to 2.5 dB after the next reversal.
- This step size is used for the remainder of the sentences in the list. The average SNR used for the final ten sentences in the list is calculated and used as an estimate of the Speech Reception Threshold (SRT) in noise.

#### Speech intelligibility with spatially separated sources

This is a Speech Reception Threshold (SRT) test with spatially separated sources consisting of a target speech signal masked by an interfering signal. The speech material was taken from the sentences VU '98 CD (Versfeld 2000), recorded from a male and a female speaker. The spatial separation between the speech and the noise is introduced by positioning two loudspeakers at -60 and +60 degrees.

#### Crescent of sound (Quentin Summerfield)

This set of tests includes spatial and presentation level roving tests and will assess localization, lateralization, head shadow and squelch effect. A set of seven loudspeakers are controlled by a cluster of eight computers, creating situations representing real-life listening conditions and which may help to differentiate the abilities of subjects from the three different groups.

### **6.3.2 Subjective**

#### Self reported benefits

Self-reported benefits in everyday listening situations will be assessed with the Speech, Spatial and Qualities Hearing Scale (SSQ) (Gatehouse 2004). The SSQ consists of three

scales that assess different domains of hearing: 1) The Speech Hearing subscale consists of 15 questions that assess the ability to separate speech from competing noise in a wide range of listening contexts, 2) The Spatial Hearing subscale consists of 17 questions that assess the ability to locate sound sources and their direction of movement, 3) The Quality of Hearing subscale consists of 19 questions that assess naturalness and clarity of sound sources. The subjects respond to each question using a rating scale that ranges from 0 (not at all) to 10 (excellent).

#### Quality-of-life questionnaires

- The *Health Utilities Index 3 (HUI3)* is a measure of general health status. It contains questions on eight domains: vision, hearing, speech, ambulation, dexterity, cognition, emotion and pain.
- *Time Trade-off (TTO)*: comprises one question about how many years of the life patients are living at the moment, they would sacrifice for living with perfect hearing for the rest of their days.
- *Visual Analogue Scale (VAS)*: comprises two 10cm scales on which patients can rate their hearing and health.
- *Euro-QoL5D*: is a measure of general health status. It contains questions on: mobility, self-care, daily activities, pain/complaints, anxiety/depression.
- The *Abbreviated Profile of Hearing Aid Benefit (APHAB)* is a 24 item, self assessment, disability based inventory to document the outcome of a hearing aid fitting and evaluate the fitting over time. The inventory yields scores on subscales for ease of communication, listening under reverberant conditions, listening in background noise and aversiveness of sound.
- The *Glasgow Benefit Inventory (GBI)* is a measure of patient benefit developed especially for otorhinolaryngological interventions (Robinson 1996). It is validated to measure outcomes on health status after otorhinolaryngological procedures. It measures QoL in three domains: social, general and physical. The domains score on a scale of -100 to 100 (minimum versus maximum benefit, respectively).
- *Hospital Anxiety and Depression Scale (HADS)*: a fourteen item screening tool for anxiety and depression in non-psychiatric clinical populations.

